#### 2.6.5. Power-Strength Training Component

Power training will include two LL exercises (seated knee extension and standing hip extension) performed using CLX looped elastic bands (TheraBand, The Hygenic Corporation, Akron, OH, USA). Participants will be instructed to execute the concentric phase with maximal intentional velocity, followed by a brief isometric pause (1 s) and a controlled eccentric phase (2 s) to ensure technical accuracy and safety.

Training intensity will be regulated by a combination of objective criteria (hand-grip position, band color; maximum stretch 300% of the resting band length) and subjective effort, monitored using the rating of perceived exertion recorded after the first repetition of each set (RPE-1). The target power training intensity will correspond to an RPE of 5–6 throughout the intervention, with band tension progressively adjusted to maintain the prescribed level of perceived exertion while enabling to perform the concentric phase with maximal intended velocity. Participants will be instructed to execute each repetition as fast as possible during the concentric phase while maintaining correct technique, as movement velocity has been identified as a key determinant of improvements in physical function [18,19].

Intensity will be monitored during each session using the OMNI-RES RPE scale for elastic band resistance exercise [47], which constitutes the primary real-time operational tool for intensity control. Exercise intensity will be adjusted by modifying elastic band resistance, grip width, exercise duration, and postural demands according to participants perceived exertion and their ability to complete the prescribed repetitions with correct technique. The %1RM values reported in the intervention tables should be interpreted solely as approximate contextual descriptors of relative training intensity to facilitate comparison with the broader resistance-training literature and do not correspond to directly measured one-repetition maximum (1RM) values for elastic resistance [47].

Training intensity will progress across the 18-week intervention following a structured periodization scheme (Table 4). During weeks 1–2, intensity will be set at approximately 60% of estimated 1RM (initial RPE: iRPE 2–3; final set RPE: fRPE 5–6). During weeks 3–7, intensity will increase to approximately 65% of estimated 1RM (iRPE 3–4; fRPE 5–6). From week 8 onwards (Weeks 8–18), intensity will be maintained at approximately 70% of estimated 1RM (iRPE 3–5; fRPE 5–6), consolidating neuromuscular adaptations prior to post-intervention assessment. These values are consistent with the progressive scheme shown in Table 4.

To consolidate technique, participants will perform 10 repetitions per set during the first two weeks and 8 repetitions thereafter. The number of sets per exercise will progress from 2 during the first 7 weeks (weeks 1–7) to 3 from week 8 until the end of the intervention (weeks 8–18), with 90 s of active recovery between sets (rhythmic swinging of the extremities, coordinative movements, along with cognitive tasks without the use of elastic bands) and 60 s of rest between exercises for hydration or sweat wiping. The power-strength exercises are described in Figure 3 and summarized in Table 4. The detailed exercise prescription and progression across the intervention period are presented in Table 5.

#### 2.6.6. Strength Training Component

This block will initially consist of four strength exercises performed in sequence during the first 7 weeks of the intervention: lateral trunk inclinations, squat with shoulder press, standing hip abduction and standing shoulder abduction in the scapula plane using CLX looped elastic bands (TheraBand, Hygenic Corporation, Akron, OH, USA). From week 8 onwards, lateral trunk inclinations will be removed, and the programme will consist of the three strength exercises: squat with shoulder press, standing hip abduction and standing shoulder abduction in the scapula plane. Training intensity will be adjusted by band tension (grip position, band color, number of bands, elongation restricted to a maximum of 300% of the resting length) and monitored with RPE at the end of the set. Participants will perform 10 repetitions per set during the first two weeks and 8 repetitions thereafter. The number of sets will progress from two during the first 7 weeks (weeks 1–7) to three from week 8 until the end of the intervention (weeks 8–18), at a target RPE of 5–9.

Training intensity in the strength block will be regulated using the RPE recorded at the end of each set, following conventional resistance training practice. This differs from the power training block, in which RPE will be assessed after the first repetition (RPE-1) to preserve movement velocity throughout the set. In the strength block, end-of-set RPE will reflect the accumulated neuromuscular fatigue generated across all repetitions, which is the relevant stimulus for strength adaptations. All exercises will be performed with a controlled concentric phase (1–2 s), a brief isometric pause (1 s), and a controlled eccentric phase (2–3 s), ensuring mechanical tension throughout the full range of motion. During the final phase of the programme (weeks 13–18), in which intensity will reach 80% of the estimated 1RM (RPE 8–9), the supervising physiotherapist will actively monitor technique execution on a repetition-by-repetition basis. Special attention will be paid to the squat with shoulder press, where accumulated fatigue may result in lumbar hyperextension during the overhead pressing phase or loss of knee alignment during the squatting phase, both of which represent potential injury risks in older adults. Sets will be terminated if technical failure is observed, regardless of whether the prescribed number of repetitions has been completed.

The number of sets per exercise will progress from two during weeks 1–7 to three during weeks 8–18, with 90 s of active recovery between sets (rhythmic swinging of the extremities, coordinative movements, along with cognitive tasks without the use of elastic bands) and 60 s of rest between exercises for hydration or sweat wiping. The introduction of low-intensity active pauses with engaging exercises will be used as a strategy to improve adherence to the program, in addition to increasing caloric expenditure and improving the cardiovascular system.

The detailed exercise prescription and progression across the intervention period are presented in Table 6.

Exercise descriptions, key cues, and safety considerations are provided in Figure 4 and Table 7.

#### 2.6.7. Aerobic and Coordination Training Component

The aerobic component will combine stationary and locomotor tasks designed to reflect everyday mobility demands and reduce fall risk, incorporation multidirectional gait patterns, changes in tempo, and brief accelerations/decelerations. Aerobic intensity will progressively increase from approximately 65% to 85% of age-predicted maximum heart rate and will be monitored using the Borg RPE scale (6–20), targeting values between 11 and 15 [50,51].

To differentiate the aerobic component from the warm-up phase, the aerobic block will incorporate more complex locomotor and coordinative task performed at moderate-to-vigorous intensity. Coordination and dual-tasks activities will be interleaved during recovery periods of the power, strength and aerobic blocks. These activities will include reaction-time drills, dance-based sequences, obstacle negotiation, and progressively complex cognitive flexibility tasks, as illustrated in Figure 5 and Table 8.

#### 2.6.8. Flexibility and Relaxation Training Component

Participants will perform diaphragmatic breathing exercises and static stretching targeting the main muscle groups. One repetition of each stretch will be held for approximately 20 s, and participants will be instructed to perceive a mild, non-painful stretching sensation during each exercise.

The flexibility exercises included in the program are illustrated in Figure 6.

#### 2.6.9. Pelvic Floor Intervention

Participants allocated to EXVERB and EXVERBPSY will standardize instruction to perform voluntary PFM contractions integrated into balance, strength, and power exercises to promote functional coordination of the PF during global motor tasks. The PFM component will include both slow (8–10 s) and fast (1–3 s) contractions. Initially, participants will practice correct PFM activation in stable positions to support selective activation and awareness. PFM activation will then be progressively integrated into standing balance tasks, emphasizing coordinated co-activation with diaphragmatic breathing and lumbopelvic control. During power and strength blocks, fast PFM contractions will be cued during functional exercises performed under increased mechanical and postural demands to reinforce coordinates PFM activation [42,52].

#### 2.6.10. Psychoeducation Intervention

The PSY sessions will be delivered by a clinical psychologist specialized in gerontology once or twice per month (six sessions total) during the 18-week intervention period. The sessions will address emotional awareness, cognitive flexibility, and understanding and regulation of emotions (e.g., stress, fear, anxiety), as well as pain and sexuality-related concerns. Session development will be informed by the Unified Protocol for Transdiagnostic Treatment of Emotional Disorders [21], supplemented with selected components from Acceptance and Commitment Therapy [22] and self-compassion-based approaches [24]. The primary aim is to improve emotion regulation through identification of emotional responses, selection of appropriate regulation strategies, and implementation of these strategies in daily life. The content and structure of the PSY sessions are summarized in Table 9. The psychoeducational sessions are theoretically grounded in three mechanisms linking psychological content to the primary clinical outcomes of this trial: (1) emotion regulation and acceptance techniques reduce experiential avoidance associated with UI and fear of falling, promoting valued-action engagement and sustained adherence to the exercise programme [21,22]; (2) self-compassion strategies reduce the psychological amplification of UI impact caused by self-critical responses to leakage episodes, improving quality of life and treatment engagement independently of symptom severity [24]; and (3) self-efficacy enhancement targets exercise adherence and UI self-management behaviours, which are established mediators of functional outcomes in older adults with UI [25]. Home-practice materials will be provided, and audio recordings of guided practices will be made available upon request to facilitate continued practice. Between-session tasks and reflective exercises will be prescribed and subsequently reviewed during the following sessions to monitor adherence and facilitate skill consolidation. Session materials and reminders will also be shared through a communication group to enhance intervention fidelity and support continued engagement.

An overview of the experimental design and intervention arms is provided in Figure 7.

To summarize, the experimental design with the training and assessment characteristics can be observed in Figure 7.

#### 2.6.11. Follow-Up and Co-Interventions

During the 6-month follow-up period, no supervised intervention sessions will be provided. Control participants will be offered access to the intervention components only after completion of the final follow-up assessment. Participants from all groups will be instructed to maintain their usual lifestyle habits, and self-reported physical activity levels will be monitored throughout the follow-up period. In addition, any co-interventions potentially affecting study outcomes, including physiotherapy treatments, PFM rehabilitation, or changes in UI related medication, will be recorded and considered during data interpretation.

### 2.7. Study Variables

Outcome measures will assess physical/functional and psychological domains. Sociodemographic and clinical variables (age, anthropometrics, obstetric history [number of pregnancies and vaginal deliveries], menopause onset, comorbidities, medication use, and lifestyle factors) will be collected at baseline. Current medications potentially affecting urinary function (e.g., diuretics and antihypertensive medications) will also be recorded. All outcome measures will be assessed at baseline, post-intervention (18 weeks), and at 6-month follow-up.

#### 2.7.1. Primary Outcome Measures

Primary end-point: Pelvic floor muscle strength

Maximal PFM strength will be assessed using vaginal manometric perineometry, and the maximal voluntary contraction pressure (mmHg) will be recorded using a validated intravaginal pressure device iEase XFT0010 (Sshenzhen XFT Medical Limited, Shenzhen, China). Vaginal manometric perineometry has demonstrated high intra-rater reliability for assessing PFM strength in women with PF disorders [53,54]. This variable was selected as the primary outcome for the a priori sample size calculation (Section 2.4) and directly addresses the primary mechanistic hypothesis of the trial (H1).

#### 2.7.2. Secondary Outcome Measures

PFM function

PFM function will be evaluated using the PERFECT assessment scheme, developed and validated by Laycock and Jerwood [55]. The following components will be assessed according to standardized procedures: Power (maximal voluntary contraction graded 0–5 using the modified Oxford scale), Endurance (duration of a sustained maximal voluntary contraction, up to 10 s), Repetitions (number of repeated sustained contractions at the same intensity, up to 10), and Fast contractions (number of rapid 1 s contractions with full relaxation between efforts, up to 10). All digital palpation assessments will be performed by the same trained physiotherapist using a standardized assessment protocol, thereby eliminating inter-rater variability. The individual PERFECT components (Power, Endurance, Repetitions, and Fast contractions) will be recorded and analysed separately as secondary outcomes. No aggregate or total PERFECT score will be calculated.

Objective assessment of PFM activation will be performed using intracavitary electromyography (iEMG), a valid and reliable method for assessing PFM neuromuscular activation in women with PF dysfunction, including UI [56]. Maximum and mean voluntary contraction amplitudes will be recorded using the NeuroTrac^®^ MyoPlus2 Pro system (Verity Medical Ltd., Hampshire, UK) with a vaginal intracavitary electrode and a surface reference electrode. To improve between-session comparability and reduce the influence of electrode placement and reinsertion variability, iEMG amplitudes will be normalized within each assessment session. Specifically, EMG activity recorded during each contraction will be expressed as a percentage of the maximum voluntary contraction obtained during the same assessment session (%MVC). Absolute amplitudes in µV will be retained for descriptive purposes, whereas normalized %MVC values will be used for longitudinal comparisons across baseline, post-intervention, and follow-up assessments.

B.Urinary incontinence patterns and impact

UI-related symptoms and voiding patterns will be assessed using a 3-day voiding diary, a widely accepted and validated clinical tool that captures urinary frequency, leakage episodes, and symptom severity in daily life contexts [57].

UI severity and its impact on quality of life will be assessed using the International Consultation on Incontinence Questionnaire–Short Form (ICIQ-SF). The ICIQ-SF is a validated and widely used instrument in older adults. Total scores range from 0 to 21, with higher scores indicating greater symptom severity [35].

C.Abdominal muscle function

Abdominal muscle morphology and activation will be assessed using ultrasound imaging to evaluate inter-recti distance and transversus abdominis (TrA) activation. Measurements will be performed with a portable ultrasound device (General Electric Logiq E V2) equipped with a linear transducer, and values will be expressed in millimeters (mm). Participants will be positioned in a supine position with the LL flexed to minimize lumbar lordosis and abdominal wall tension. Inter-recti distance will be measured with the transducer placed transversely at standardized locations 1 cm above and 1 cm below the umbilicus. Measurements will be obtained under two conditions: at rest and during forced exhalation, corresponding to the activation phase of diaphragmatic breathing. The difference between conditions will be used to quantify changes in rectus abdominis separation.

Bilateral TrA activation will be assessed with the transducer positioned transversely along the mid-axillary line, midway between the iliac crest and the costal margin. Measurements will be performed at rest and during forced exhalation, and changes in muscle thickness between conditions will be used as an indicator of TrA activation. Ultrasound imaging has been shown to be a valid and reliable method for assessing abdominal muscle morphology and activation patterns in clinical and research settings [58,59].

D.Gait and aerobic capacity

Gait speed will be assessed using the 4-Meter Walk Test (4MWT) at usual and maximal walking speeds. To minimize acceleration effects, participants will start walking 0.5 m before the first marker and continue walking 0.5 m beyond the end marker. The time required to complete the central 4 m will be recorded, and gait speed will be calculated in meters per second (m/s) [60]. The 4MWT is a widely used and validated measure of functional mobility in older adults, demonstrating good reliability and strong clinical relevance [61].

Aerobic capacity will be evaluated with the Six-Minute Walking Test (6MWT) following standardized guidelines [62]. Gait biomechanics during walking will be assessed using Runscribe^TM^ inertial sensors (Scribe Labs, Moss Beach, CA, USA) placed on both feet, providing spatiotemporal parameters (speed, cadence, stride length, and gait cycle duration for the left and right foot) [63].

E.Lower-Limb muscle power

LL muscle power will be assessed using a Chronojump^®^ contact platform through vertical jumps tests, including the Countermovement Jump (CMJ) and the Abalakov Jump (ABK), which are sensitive to changes in muscular power in older adults [64,65].

LL muscle power will also be evaluated using a Chronojump^®^ linear encoder during two resistance exercises (squat and leg extension). Participants will perform one familiarization repetition followed by two sets of five repetitions for each exercise, with a one-minute rest between sets. All repetitions will be executed with maximal intentional concentric velocity. The Chronojump^®^ system has demonstrated high concurrent validity for displacement and velocity measurements in older adults (r > 0.94) [66]. All assessments will be conducted under standardized safety conditions, including close supervision by trained personnel and the use of protective measures when necessary. Participants presenting pain, dizziness, instability, or any contraindication to maximal effort testing will not perform the corresponding test.

F.Physical function of upper and lower limb

Functional LL performance will be assessed using the Five Times Sit-to-Stand (5tSTS) and the Thirty-Second Sit-to-Stand (30sSTS) tests, both validated and reliable measures of functional strength and physical performance in older adults [61,67,68]. Upper-limb muscle strength will be evaluated using 30 s Arm Curl Test, performed bilaterally, with the number of completed repetitions recorded for each arm [67].

G.Maximal isometric muscle strength

Maximal isometric muscle strength will be assessed using a Chronojump^®^ traction force sensor dynamometer (Chronojump^®^ Boscosystem, Barcelona, Spain), fixed to rigid structures to ensure mechanical stability. Force output will be recorded in newtons (N) and analyzed using the corresponding software (Chronojump^®^ Boscosystem, version 2.3.0-2629-x64).

The same standardized testing positions, dynamometer attachment points, and body alignment will be maintained across all assessments to ensure comparability within-participant over time. Force values are reported in newtons (N) and are not intended to represent joint torque. Isometric strength will be assessed bilaterally for the following muscle groups: knee extension, hip flexion, hip extension, hip abduction, hip adduction, and trunk (spine) extension. For each muscle group, participants will first perform one brief familiarization contraction (≈1 s) followed by two maximal isometric contractions of 5 s, with a 1 min rest between trials. Standardized testing positions and verbal instructions will be used across participants, and the order of muscle group testing will be counterbalanced to minimize fatigue effects. The mean value of the two maximal trials will be used for statistical analysis. For bilateral muscle groups, the left and right limbs be assessed, recorded, and analysed separately; therefore, no average bilateral value will be calculated. Detailed descriptions of the standardized testing positions, participant stabilization, dynamometer placement, testing sequence, and measurement procedures for each muscle group are provided in Supplementary Material S1. Participants will be stabilized using standardized body positioning and manual supervision when required to minimize compensatory trunk and pelvic movements during testing.

Upper-limb maximal isometric strength will be assessed using a digital handgrip dynamometer (Takei TKK 5401, Takei Scientific Instruments Co., Ltd., Tokyo, Japan). Participants will perform three maximal contractions with each hand, and the mean value will be used for analysis. Handgrip strength will be expressed in kilograms (kg) and has demonstrated high reliability in older adult populations [69].

H.Balance performance

Balance performance will be assessed using clinical and instrumental measures. Proactive balance will be evaluated with the Functional Reach Test [70,71], and dynamic balance with the Timed Up and Go test [72].

Static balance will be assessed using the Modified Romberg Test (participants will be held for 10 s without compensatory movements of the upper limbs or trunk) [61] and single-leg stance [73].

Additionally, static posturography will be used to analyze center-of-pressure (COP) displacement under different sensory conditions using the NedSVE/IBV^®^ system on a Dinascan/IBV force platform. The following COP variables will be collected: sway area (mm^2^) and maximum anteroposterior (AP) and mediolateral (ML) displacement (mm). Static posturography have demonstrated good clinical utility and moderate-to-high test–retest reliability in bipedal standing tasks under different sensory conditions [74,75].

I.Fear of falling

Fear of falling will be assessed using the short Falls Efficacy Scale–International (FES-I). In the present study, a shortened and validated Spanish version will be used, which assesses confidence in performing daily 7 activities associated with balance demands and fall risk. Higher total scores indicate greater concern about falling. This version has demonstrated adequate psychometric properties in Spanish-speaking populations [76]. Total scores will be used for statistical analysis.

J.Quality of life

Health-related quality of life will be assessed using the 36-Item Short Form Health Survey (SF-36), which evaluates eight domains of physical and mental health. Domain scores range from 0 to 100, with higher scores indicating better perceived health status and quality of life [77].

K.Psychological and social well-being

Self-esteem will be assessed using the Rosenberg Self-Esteem Scale (RSES), a widely used measure of global self-esteem. The scale consists of 10 items rated on a 4-point Likert scale, with total scores ranging from 10 to 40, and higher scores indicating higher self-esteem [78].

L.Physical Activity Questionnaire-Short Form (IPAQ-SF)

Physical activity levels will be assessed using the IPAQ-SF, a validated self-report questionnaire which records physical activity performed during the previous 7 days. Data will be processed according to the official IPAQ scoring protocol and expressed as total physical activity (MET-min/week). Participants will also be classified into the standard IPAQ physical activity categories (low, moderate, or high). Data cleaning and truncation procedures will follow the official IPAQ data processing guidelines. The IPAQ-SF will be administered at baseline (T0) and at the 6-month follow-up assessment (T2).

M.Body weight and composition

Body weight will be measured in kilograms (kg). Body composition parameters, including fat mass and lean mass percentages, will be assessed using bioelectrical impedance analysis (BIA) with a validated analyzer (Tanita^®^ BC-545N MA, Tokyo, Japan).

N.Height

Height will be measured to the nearest 0.1 cm using a calibrated stadiometer (SECA 217, Seca GmbH & Co., Hamburg, Germany), with participants standing barefoot in an upright position.

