### Limitations

The present protocol has several limitations that should be acknowledged.

(i)The active intervention groups receive substantially more participant–therapist contact than the educational control group (36 supervised exercise sessions vs. four monthly educational sessions), which may contribute to observed between-group differences beyond the specific intervention components. The control condition was intentionally designed to reflect realistic community practice rather than an attention-matched control, and the educational sessions provided to this group, covering healthy ageing, fall prevention, and pelvic floor health, may have improved participants’ knowledge and health-related behaviours, potentially affecting some outcomes, although they were not expected to produce the specific physiological adaptations associated with supervised exercise.(ii)The sample size was calculated exclusively based on the primary endpoint (maximal voluntary contraction pressure assessed by manometric perineometry). Accordingly, this trial may not be adequately powered to detect smaller between-group differences in secondary outcomes or in the pre-specified subgroup analyses according to UI subtype. These analyses should therefore be considered exploratory and hypothesis-generating.(iii)The study is restricted to community-dwelling older women, limiting generalizability to institutionalised populations or men.(iv)Intracavitary EMG amplitudes will be normalised to within-session MVC (%MVC) to reduce inter-session variability; however, this approach does not fully eliminate variability arising from training-induced changes in MVC neuromuscular characteristics, and longitudinal iEMG findings should be interpreted with appropriate caution.(v)Movement velocity during power training sessions will not be directly monitored; although the maximum intended velocity instruction and RPE-based intensity targets provide operational control of the training stimulus, confirmation that participants trained within the intended velocity range on a repetition-by-repetition basis is not possible.(vi)Falls and near-falls will not be prospectively recorded during the intervention or follow-up period; future trials in this population should be adequately powered to include fall incidence as a primary endpoint alongside functional and psychological outcomes.(vii)The a priori sample size was estimated using a repeated-measures ANOVA approximation in G*Power 3.1 [43], as dedicated LMM-specific power calculators are not readily available; under the assumed compound-symmetry covariance structure this approximation is considered conservative and reproducible, but represents a minor methodological limitation of the a priori calculation.

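### Same-session %MVC fixes the maximum iEMG amplitude at 100% and turns the mean into a mean-to-peak ratio, so the longitudinal iEMG analysis cannot measure a gain in activation

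*Protocol article*

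**What the plan says.** All of this is in the protocol article.

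- **Quantities recorded** (section 2.7.2, PFM function): "Maximum and mean voluntary contraction amplitudes will be recorded" with a vaginal electrode. No other iEMG quantity is named.
- **Reason for normalising** (same section): "To improve between-session comparability and reduce the influence of electrode placement and reinsertion variability, iEMG amplitudes will be normalized within each assessment session".
- **Denominator** (same section): "EMG activity recorded during each contraction will be expressed as a percentage of the maximum voluntary contraction obtained during the same assessment session (%MVC". The reference is therefore set anew at each of T0, T1 and T2.
- **Scale used over time** (same section): "Absolute amplitudes in µV will be retained for descriptive purposes, whereas normalized %MVC values will be used for longitudinal comparisons across baseline, post-intervention, and follow-up".
- **Model** (section 2.8.1): every secondary outcome goes through the same mixed model as the primary endpoint, with the group × time interaction and five Holm-corrected contrasts at T1 and again at T2.
- **The plan's own caveat** (Limitations, item iv): "this approach does not fully eliminate variability arising from training-induced changes in MVC neuromuscular characteristics", followed by a call for caution with longitudinal iEMG findings.

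**The concern.** The iEMG measure is offered as the objective assessment of pelvic floor muscle activation. Activation instruction is the component that separates EXVERB from EX, so a reader will look to this outcome for evidence that the instruction changed activation.

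Dividing by the maximum contraction of the same visit means that the yardstick moves with the thing being measured. If training raises the maximum, numerator and denominator rise together. The maximum then carries no information over time. The mean answers a different question: how close the average amplitude comes to that day's peak.

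At stake is model-based inference on this one secondary measure. A flat or falling mean %MVC would say little about whether activation had improved, yet it is the value that would be tested and tabulated with effect sizes.

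**Working it through.** The plan gives no sample size, power or expected value for iEMG, so there is no figure to reproduce. The check is algebra on the plan's definitions, followed by illustrations. The amplitudes, gains and SDs below are assumptions, not figures from the documents.

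**Definition.** At visit t, %MVC(t) = 100 × A(t) / MVC(t), where A is the recorded amplitude and MVC is the maximum of the same session.

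**Maximum amplitude.** On the plain reading A(t) = MVC(t), so %MVC(t) = 100 for every woman at every visit. Variance and change are both zero, and a mixed model has nothing to fit. This needs no assumption about effect size or SD.

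**Mean amplitude.** %MVC(t) = 100 × mean(t) / max(t). If training multiplies both by g, then 100 × (g × mean) / (g × max) = 100 × mean / max, and g drops out.

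**Illustration.** Assumed baseline: maximum 20 µV, mean 12 µV, so mean %MVC = 12/20 = 60%.

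| Change | Maximum µV | Mean µV | Maximum %MVC | Mean %MVC |
|---|---|---|---|---|
| both ×1.2 | 24 | 14.4 | 100 | 14.4/24 = 60 |
| both ×1.5 | 30 | 18 | 100 | 18/30 = 60 |
| both ×2.0 | 40 | 24 | 100 | 24/40 = 60 |
| max ×1.5, mean ×1.2 | 30 | 14.4 | 100 | 14.4/30 = 48 |
| max ×1.5, mean ×1.8 | 30 | 21.6 | 100 | 21.6/30 = 72 |
| max ×1.3, mean unchanged | 26 | 12 | 100 | 12/26 = 46 |

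The first three rows show cancellation. In the fourth, both amplitudes rise and the analysed value falls by 12 percentage points.

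**What this does to a test.** A simulation of 4,000 trials compared two arms of 30 at one post-intervention visit (two-sided 0.05). One arm had a 1.5-fold gain in maximum and mean, the other none. Log-SDs were 0.4 between women and 0.2 for electrode placement.

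- Log µV (maximum): gain detected in about 93% of runs.
- Mean %MVC: rejected in about 5% of runs, which is the null rate.
- Maximum %MVC: zero variance in every run.

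**How far the 93% depends on reinsertion noise.** With total log-SD s = √(0.4² + e²), d = ln(1.5)/s = 0.405/s, and a two-sample t-test with 30 per arm (noncentrality d × √15):

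| Placement log-SD e | s | d | Power on log µV |
|---|---|---|---|
| 0.2 | 0.447 | 0.907 | 93% |
| 0.4 | 0.566 | 0.717 | 78% |
| 0.6 | 0.721 | 0.562 | 57% |

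Reinsertion noise can cost a good deal of power. Mean %MVC stays at about 5% in all three rows, because a proportional gain has cancelled before the test is made.

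**The case against.** **Only a proportional gain cancels from the mean.** This stands. A reader might infer that any training effect disappears from both iEMG measures. The definitions do not support that: mean %MVC moves when mean and maximum change by different factors. The narrower criticism is that the movement is not a measure of activation gain and can have the wrong sign.

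**The reference contraction is not fully described.** Also fair. The article does not say how many contractions are recorded, or whether the MVC is a separate trial or an average, and the full protocol may. With a separate reference, maximum %MVC would scatter near 100% and a model could be fitted. The text describes no such reference, however, and a gain shared by the two contractions would still divide out.

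**The gain is not hidden, because µV is kept.** This stands in part. Section 2.8.1 promises descriptive statistics at each visit, so a rise in µV by arm could be seen. A reader might infer that the trial will be blind to a change in activation; that is too strong. What is missing is a tested between-group estimate on that scale.

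**Limitation (iv) already warns the reader.** It does ask for caution, so one cannot assume that a null result would be reported as no change in activation. But it describes the training-induced change in MVC as leftover variability, when that change is the signal being divided out. It does not say that the maximum is constant, and it leaves the choice of analysis scale as it is.

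**Normalisation has a stated purpose.** Electrode placement and reinsertion do add noise to µV. Randomisation guards against bias from this but does not restore precision, and the documents give no variance from which to size the loss. Log µV is therefore not free, and a reference that training does not change would be another route.

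**Conclusion.** The concern holds for the scale chosen for the longitudinal iEMG comparisons.

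- **Maximum %MVC** is 100% at every visit on the plain reading, or near 100% with a separate reference contraction. It cannot show a group × time effect. The exact 100% rests only on numerator and denominator being the same quantity.
- **Mean %MVC** is a mean-to-peak ratio. Complete cancellation rests on mean and maximum rising by the same factor. Otherwise the ratio can rise or fall, including a fall when both amplitudes rise. It should not be read as activation gain.
- **Absolute µV**, the scale that carries the gain, is left to description.

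The reach is limited to one secondary outcome, and section 2.8.1 already treats secondary findings as supportive. The primary endpoint is manometric pressure in mmHg, and the PERFECT components are analysed separately; neither is affected. A reader might infer that the trial's conclusion on pelvic floor strength is compromised; nothing in the documents supports that. The simulated detection rates illustrate the mechanism under assumed inputs and do not estimate the power of this trial.

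**What to change.** 1. Drop maximum %MVC as a longitudinal outcome.
2. Analyse absolute amplitude, as log µV for maximum and mean, in the planned cLDA model with T0 as the first repeated measure and the same five contrasts.
3. Keep mean %MVC as a descriptive mean-to-peak ratio, with a statement that it is not read as activation gain.
4. Reword limitation (iv) to say that same-session normalisation divides out a proportional training gain, and that µV is analysed for this reason at the price of more between-session noise.

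State the MVC reference contraction in the same edit, and settle the change before allocation is unblinded.

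The cost is small: µV is already recorded, so no new measurement or visit is needed. The downside is extra noise from electrode reinsertion, which lowers precision but should not bias the randomised comparison.
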